### Data monitoring and safety

A DSMC will be made up of an independent intensivist, an epidemiologist and a statistician. They will confer after 100 patients have been enrolled and will review the unblinded data to determine the need for early termination of the trial. Early termination will be decided on the basis of either (1) safety concerns with the ongoing review of all severe adverse events (SAEs) and suspected unexpected severe adverse reactions (SUSAR) or (2) outstanding benefits. The DSMC will report to the research committee and make a recommendation after its review. A similar interim analysis will be performed at the midpoint of the study after enrolment of 400 patients.

The Haybittle-Peto stopping rule will be used in both analyses. Thus, if there is a probability of less than 0.001 in either direction that the treatment and placebo are different, the DSMC will recommend that the study be ceased.

Melatonin has no serious adverse reactions documented in the medical literature [51]. An AE caused by either melatonin or its solution will be considered as any untoward medical occurrence in a patient enrolled in this study, regardless of its causal relationship to the study treatment. AEs will be monitored with a checklist of symptoms commonly associated with medications, including headache, gastrointestinal symptoms, lethargy, myalgias and skin symptoms.

Melatonin has a very safe therapeutic profile. Assessment and documentation of AEs will be carried out by the principal and associate investigators and will be included in the data collection instrument. Once collected, these will be reviewed and classified as AEs, SAEs or SUSARs. The DSMC will have access to this information as unblinded data.

The baseline mortality of ICU patients enrolled in trials will be high because of the critical illness necessitating admission. New organ failure in a high proportion of ICU patients is not unexpected, regardless of optimal treatment and study intervention. As such, and in keeping with the advice of Cook and colleagues, events that are part of the natural history of the primary disease process or expected complications of critical illness will not be reported as SAEs in this trial unless they are thought to be causally related to the study intervention [52].

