## Abbreviations

AE: Adverse event
CAM-ICU: Confusion Assessment Method for the ICU
CAM-S: Confusion Assessment Method for delirium severity
CRF: Case report form
D/C: Discharge
DSMC: Data and safety monitoring committee
ICU: Intensive care unit
LOS: Length of stay
NCAT: NSW Civil and Administrative Tribunal
PRE-DELIRIC: Prediction of delirium in ICU patients
Pro-MEDIC: Prophylactic Melatonin for Delirium in Intensive Care
RCSQ: Richards-Campbell Sleep Questionnaire
REM: Rapid eye movement
SAE: Severe adverse event
SPIRIT: Standard Protocol Items: Recommendations for Interventional Trials
SUSAR: Suspected unexpected severe adverse reaction

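### The adverse event definition both requires and disclaims a causal link to the study drug, and SAE and SUSAR are spelled out as severe where the terms denote seriousness

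*Protocol article*

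**What the plan says.** All the operative text is in the protocol article, Methods, Data monitoring and safety. The AE sentence opens "An AE caused by either melatonin or its solution will be considered as any untoward medical occurrence in a patient enrolled in this study" and closes "regardless of its causal relationship to the study treatment". The next sentence says how events are found: "AEs will be monitored with a checklist of symptoms commonly associated with medications". The examples given are headache, gastrointestinal symptoms, lethargy, myalgias and skin symptoms.

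The first ground for early termination is "safety concerns with the ongoing review of all severe adverse events (SAEs) and suspected unexpected severe adverse reactions (SUSAR"). The abbreviation list repeats the wording: "SAE: Severe adverse event" and "SUSAR: Suspected unexpected severe adverse reaction". The word *serious* occurs once in the section, in a statement about the literature: "Melatonin has no serious adverse reactions documented in the medical literature".

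The section also says that:

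- the principal and associate investigators assess and document AEs;
- collected events are afterwards reviewed and sorted into AEs, SAEs or SUSARs, by a party that is not named;
- the data and safety monitoring committee (DSMC) sees this information unblinded;
- natural-history events and expected complications of critical illness are exempt from SAE reporting unless thought to be caused by the intervention.

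**The concern.** There are two separate faults of wording.

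The first is causality. An AE and an adverse reaction are different things: the first carries no causal condition, the second does. The sentence merges them. One reader would record only events attributed to the study drug. Another would record every untoward event, and the opening words would then label all of them as drug-caused.

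The second is seriousness. Severity grades intensity; seriousness describes consequence, such as death, threat to life, prolonged stay or disability. An intense symptom may have no consequence, and a moderate event may prolong the stay. If *severe* is taken at face value when events are classified, the set called SAE differs from the set that the term normally denotes.

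At stake is the meaning of the safety counts that the DSMC reviews and that the trial will publish. If those who record events read the text differently, the counts mix two quantities, and some events of interest may not be recorded at all.

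**Working it through.** No figure in the plan is in question and no arithmetic applies. The check sets the statements side by side.

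**1. Is the AE sentence contradictory?** The opening phrase of "An AE caused by either melatonin or its solution will be considered as any untoward medical occurrence in a patient enrolled in this study" makes causation by the drug or its solution a condition. The closing phrase, "regardless of its causal relationship to the study treatment", makes causation irrelevant. The two cannot both govern whether an event is recorded, so the contradiction is confirmed within one sentence.

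**2. Does the surrounding text settle the meaning?** It points both ways.

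- The checklist of medication-type symptoms leans towards drug-related events, and is narrower than an all-embracing definition of AE.
- The reference to any untoward occurrence leans towards all events.
- The unblinding paragraph under Allocation, randomisation, compliance and blinding treats a doctor's view that the drug is causing an AE as a judgement about that AE. This would be redundant if every AE were drug-caused by definition, so it also leans towards the causality-free reading.
- The exemption for complications of critical illness has its own causality condition, but applies it to SAE reporting only.

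The causality-free reading is the more natural one, but the text does not fix it.

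**3. Is *severe* a single slip?** No. It is used for both terms in Data monitoring and safety ("severe adverse events (SAEs) and suspected unexpected severe adverse reactions (SUSAR") and for both again in Abbreviations, so all four expansions agree. Yet the same section uses *serious* for reactions in the literature and never relates the two words.

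**4. Does this reach a decision?** By steps:

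- Investigators document AEs.
- The collected events are then classified as AEs, SAEs or SUSARs.
- Review of SAEs and SUSARs is the safety ground for early termination, at DSMC reviews set after 100 and after 400 patients.

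The AE sentence thus stands upstream of the stopping review. A later classification step can relabel what was recorded. It cannot recover an event that was never recorded because it was not attributed to the drug.

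**5. Direction of any error.** The investigators and the ICU doctors and nurses are blinded, so differences in reading should fall on both arms alike. The expected effect is noise and lost events, not a shift towards either arm.

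**6. What is protected regardless?** Under Morbidity and mortality, the article records deaths at 28 and 90 days, ventilator-free days, vasopressor use, renal replacement therapy, re-intubation, tracheostomy and organ failure scores. Table 1 adds liver function tests and length of stay. None of these depends on an AE label.

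**7. Size.** The documents give no AE rate under either reading and no information on how sites would divide. Any figure for the distortion would be invented.

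**The case against.** The strongest reply is that this is a drafting matter with limited consequences. Much of that stands.

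- *A common checklist and data collection instrument limit divergence.* This is correct. The documents do not show that sites will differ, and the unnamed classification step may be central. Inconsistent recording is a plausible risk, not an established fact.
- *SAE and SUSAR are not defined as severe events.* Also correct. A reader might infer that, as written, a severe headache is an SAE and a moderate event that prolongs the ICU stay is not. The article does not support this: *severe* appears only in the expansion of abbreviations, with no intensity grade and no operational criteria. Those criteria may be in the full protocol, and their absence from an article is no fault. What stands is that the word used is the wrong one.
- *The stopping review does not run on AE counts.* This is partly right. The safety ground names SAEs and SUSARs, and SAEs have their own causality rule. But both are drawn from collected AEs, so the AE sentence still matters.
- *Early termination does not rest on these events alone.* True. The section has a second ground, outstanding benefit, and a Haybittle-Peto threshold of 0.001 in either direction. Mortality is recorded whatever the AE classification.
- *Recording every untoward event in ICU patients would be a heavy burden.* True, and the correction has to avoid it.

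**Conclusion.** The point holds as a specific error of wording in operative safety text. The AE sentence contradicts itself, and the expansions of SAE and SUSAR use a word for intensity where the terms denote seriousness. Until both are corrected, AE and SAE counts may be recorded inconsistently and be hard to interpret.

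The size is modest and cannot be quantified from the documents. The sample size, alpha, interim threshold and primary analysis are untouched, and no bias towards an arm is expected while blinding holds.

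A reader might go further and conclude that the published AE rate will be meaningless, or that the stopping decision will turn on how each site reads the sentence. The documents do not support either conclusion, because of the shared checklist, the later classification step and the separate recording of deaths and organ support.

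The verdict assumes that investigators work from wording like that in the article. If the full protocol or the case report form already gives one AE meaning and standard seriousness criteria, only the article needs correcting.

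**What to change.** 1. In Data monitoring and safety, delete the opening causal phrase from the AE sentence, so that an AE carries no causality condition.
2. Record the blinded investigator's view of relatedness to the study drug as a separate judgement on each event.
3. Keep the existing checklist as the means of capture, and keep the existing exemption for natural-history events and expected complications of critical illness, so that workload does not grow.
4. Replace *severe* with *serious* in SAE and SUSAR, in Data monitoring and safety and in Abbreviations, matching the seriousness criteria that the full protocol uses. Keep intensity as a separate item.

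The cost is a wording amendment and brief site retraining. The form may need added items for relatedness, seriousness or intensity if it lacks them; it is not shown. Because the article reports that recruitment is under way, AE recording may differ slightly before and after the change. The amendment date should be noted so that this can be seen when AEs are reported.

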### Ethics and dissemination

Ethics approval has been sought and obtained from the Sir Charles Gairdner Hospital Human Research Ethics Committee in Western Australia and the Hunter New England Human Research Ethics Committee in New South Wales. The NSW Civil and Administrative Tribunal (NCAT) has granted approval to conduct the clinical trial in this state. Protocol amendments will be communicated to these ethics committees for approval.

Subject confidentiality is strictly held in trust by the investigators and is extended to clinical data collected and test results. No information will be released to any third party without the prior written approval of the participating institutions. Clinical data will not be released without the written permission of the participating individuals, except for the DSMC where required. Data will be identified only by the study’s subject identification number.

This study protocol has been written following the Standard Protocol Items: Recommendations for Interventional Trials (SPIRIT) checklist (Additional file 1). A populated checklist (Table 1) and a figure (Additional file 1) displaying the schedule of enrolment, interventions and assessments have been provided. The results of this trial will be written as an article that will be submitted to peer-reviewed medical journals for publication.

### Consent

Informed consent will be obtained from the patients or, when it is not possible for patients to consent for themselves, from their person responsible. The investigators received approval from the NCAT to allow the inclusion of patients who are highly dependent on medical care. In Western Australia, the study will be undertaken using an emergency waiver of consent, as allowed for in the National Health and Medical Research Council national statement, in conjunction with acknowledgement from the patient’s person responsible that he or she is not aware of any reason why the patient would have chosen not to participate. All patients will be followed and given the opportunity to consent to continue in the study once their capacity to consent is regained [53].

## Discussion

Delirium is increasingly being recognised as a significant issue in hospital and particularly in ICU. It is associated with poorer outcomes for the patients, their families and the wider community. Intensive care is an area where the prevalence of delirium is higher than in the general wards. There are multiple potentially modifiable risk factors but very limited effective pharmacological options for either prevention or treatment.

To our knowledge, this trial will be the largest trial evaluating melatonin as a prophylactic agent for delirium in any setting, and certainly the largest in intensive care. It will also be one of the larger trials evaluating any prophylactic agent in intensive care. Currently, a trial by van den Boogaard and colleagues is recruiting. They are evaluating haloperidol as a preventative agent for ICU delirium and plan to enrol 2145 patients into 3 arms. However, haloperidol has potential side effects, whereas melatonin is extremely safe, inexpensive and potentially more acceptable to patients, with the rate of side effects being less than placebo [51].

The polysomnography arm will be an insightful explanatory component of the study and, to our knowledge, will be one of the largest series of polysomnography in the ICU setting. It may open up further avenues for research into sleep in critical care.

The choice of 4 mg of melatonin as a dose required some consideration. The existing trials have used a variety of doses ranging from 0.5 mg to 5 mg [37–39, 41]. Bourne and colleagues [54] used 10 mg to aid sleep and found a carry-over effect to the following day. Therefore, we feel that 4 mg is a practical dose within the range of previous studies. Evidence exists confirming absorption in critical care for similar doses, and this dose is unlikely to have a significant carry-over effect the following day. Melatonin (Circadin; Flynn Pharma, Dublin, Ireland), the current Pharmaceutical Benefits Scheme listed agent, also comes in 2-mg tablets.

Patients will be assessed for delirium on enrolment. This will not be possible where patients arrive at the unit ventilated and heavily sedated. Because of this, true incidence will not be able to be established, and it is recognised that some patients may already have delirium on enrolment. The investigators feel it is important to keep this a pragmatic trial. The decision to mandate that patients be enrolled within 48 h of their ICU admission was made to ensure that the study drug is given early in patients’ stay.

The enrolment of patients who have an expected LOS longer than 72 h is being done because patients with increased LOS are more likely to develop delirium. Although prediction tools for delirium do exist [55, 56], they are complex, and we seek to maintain the generalisability of our findings to a broad range of ICU patients.

### Trial status

We are in the process of recruiting patients.

## Abbreviations

AE: Adverse event
CAM-ICU: Confusion Assessment Method for the ICU
CAM-S: Confusion Assessment Method for delirium severity
CRF: Case report form
D/C: Discharge
DSMC: Data and safety monitoring committee
ICU: Intensive care unit
LOS: Length of stay
NCAT: NSW Civil and Administrative Tribunal
PRE-DELIRIC: Prediction of delirium in ICU patients
Pro-MEDIC: Prophylactic Melatonin for Delirium in Intensive Care
RCSQ: Richards-Campbell Sleep Questionnaire
REM: Rapid eye movement
SAE: Severe adverse event
SPIRIT: Standard Protocol Items: Recommendations for Interventional Trials
SUSAR: Suspected unexpected severe adverse reaction
